# Mortality impact of an increased blood glucose cut-off level for hypoglycaemia treatment in severely sick children in Malawi (SugarFACT trial): study protocol for a randomised controlled trial

**DOI:** 10.1186/s13063-017-2411-8

**Published:** 2018-01-11

**Keywords:** Hypoglycaemia, Critical care, Paediatrics, Emergency medicine

## Abstract

**Background:**

Mortality in children remains high in sub-Saharan African hospitals. While antimalarial drugs, antibiotics and other definitive treatments are well understood, the role of emergency care with supportive therapies, such as maintaining normal glucose and electrolyte balances, has been given limited attention. Hypoglycaemia is common in children admitted to hospital in low-income settings. The current definition of hypoglycaemia is a blood glucose level < 2.5 mmol/L in a well-nourished child. Outcomes for these children are poor, with a mortality rate of up to 42%. An increased mortality has also been reported among acutely ill children with low-glycaemia, defined as a blood glucose level of 2.5–5.0 mmol/L. The reason for increased mortality rates is not fully understood. This proposal is for a randomised controlled trial to determine the impact on mortality of a raised treatment cut-off level for paediatric hypoglycaemia.

**Methods:**

A total of 1266 severely ill children (age range = 1 month – 5 years) admitted to Queen Elizabeth Central Hospital in Blantyre, Malawi with blood glucose in the range of 2.5–5.0 mmol/L will be randomised into intervention or control groups. The intervention group will be treated with an intravenous bolus of 10% dextrose 5 mL/kg followed by a dextrose infusion in addition to standard care while the control group will receive standard care only. Children will be followed until discharge from hospital or death.

**Discussion:**

The first patient was enrolled in December 2016 and the expected trial deadline is January 2019. This study is the first to evaluate the benefits of increased dextrose administration in children presenting to hospital with low-glycaemia. The findings will inform national and international policies and guidelines for the management of children with blood sugar abnormalities.

**Trial registration:**

ClinicalTrials.gov, NCT02989675. Registered on 5 December 2016.

**Electronic supplementary material:**

The online version of this article (10.1186/s13063-017-2411-8) contains supplementary material, which is available to authorized users.

## Background

More than six million children aged < 5 years die each year in low-income countries, the majority due to treatable infectious diseases with pneumonia, diarrhoea and malaria as the main killers [1]. While the management of children in African hospitals and health centres routinely involves the administration of antimalarial drugs, antibiotics and other definitive treatments, the role of emergency care with supportive treatments, such as oxygen, fluids and glucose, has received less attention [2, 3]. Hypoglycaemia is known to be associated with poor clinical outcome and long-term negative effects on neurodevelopment [4]. Most low-income settings lack the capacity for rapid laboratory confirmation of hypoglycaemia and the presenting symptoms are often unspecific, such as drowsiness, agitation, hypothermia and seizures. The World Health Organization (WHO) currently defines paediatric hypoglycaemia as a blood glucose level < 2.5 mmol/L (or < 3 mmol/L in a severely malnourished child) [5]. A blood glucose level above these limits is considered adequate for sufficient energy supply for vital functions and particularly to the brain, which is dependent on glucose metabolism.

Previous studies have shown that 1.8–7.3% of children admitted to hospital in sub-Saharan Africa are hypoglycaemic [6–9]. In a recent study from north-eastern Tanzania, hypoglycaemic children had an increased risk of death with a mortality rate of as much as 42% [6]. That study and others in similar settings have also showed an increased mortality in children with low-glycaemia, defined as a blood glucose level of 2.5–5.0 mmol/L, leading to a questioning of the current cut-off for hypoglycaemia [6, 9, 10]. In children with an emergency sign, as defined in the WHO Pocket Book of Hospital Care for Children [5], and low-glycaemia, the mortality was 15% compared to 6% mortality for those with an emergency sign and blood glucose > 5.0 mmol/L (personal communication [name] 2015).

Plasma glucose concentration is maintained by the interplay of the glucose-lowering action of insulin and the glucose-raising actions of the four counter-regulatory hormones cortisol, catecholamines, glucagon and growth hormone. The counter-regulatory response has been shown at plasma levels ≤ 3.8 mmol/L [11]. In acute illness, the normal physiological response is the release of stress hormones such as cortisol, which activates the release of glucose into the blood, consequently increasing the blood glucose levels and causing hyperglycaemia.

Paediatric neuro-endocrine responses in critical illness have not been studied in detail, although several differences in the host response in children compared to adults have been suggested [12]. The ‘natural hyperglycaemia’ occurring in critical illness due to the release of stress hormones could potentially be beneficial: the higher glucose concentration compensating for a decreased or dysfunctional circulation. The child with low-glycaemia may, therefore, be a result of late care-seeking or more severe illness leading to an abnormal stress response [13] and a ‘pre-hypoglycaemic stage’. Alternatively, the lack of an increased blood glucose level may be a result of failure to use alternative sources of energy such as ketone bodies [14], infection with specific pathogens, prolonged fasting during the illness period and/or a sub-optimal nutritional status before the illness. These children may benefit from increased glucose administration.

The current cut-off level for treating hypoglycaemia (<2.5 mmol/L for well-nourished children or < 3.0 mmol/L for severely malnourished children) is based on pathophysiological assumptions that lack robust evidence. This study will report the effect of therapeutically targeting low-glycaemia, in other words the study tests raising the cut-off for treating low blood glucose from < 2.5 mmol/L to < 5.0 mmol/L.

## Methods

### Specific objectives

I.To determine the impact on in-hospital mortality of administering dextrose to severely ill children aged 1 month to 5 years with low-glycaemia at arrival to the emergency departmentII.To determine the impact on 24-h mortality of administering dextrose to severely ill children aged 1 month to 5 years with low-glycaemia at arrival to the emergency department

### Trial design

This is a single-centre, non-blinded, two-arm randomised controlled trial that will compare the impact of dextrose treatment in children with WHO emergency signs admitted to hospital with low-glycaemia. The present paper is written according to the Standard Protocol Items: Recommendations for Interventional Trials (SPIRIT) 2013 Statement for reporting a clinical trial protocol [15–17]. The SPIRIT Checklist is provided as Additional file 1.

### Trial setting

Queen Elizabeth Central Hospital is a large university hospital in Blantyre, Malawi. The hospital serves a predominately rural population and manages 23,000 paediatric admissions annually (personal communication [name] 2015). The Emergency Triage, Assessment and Treatment (ETAT) protocol [18] was developed in Queen Elizabeth Hospital and is used as the standard for management of sick children. Children will be recruited from the Paediatric Emergency Department at Queen Elizabeth Central Hospital.

### Participants

All children arriving to the emergency department for admission to Queen Elizabeth Central Hospital in Blantyre, Malawi will be screened for the presence of the following inclusion and exclusion criteria.

#### Inclusion criteria

Age range of one month to 5 yearsParent/carer willing and able to give consentPresence of one or several emergency signs [5]^1^○ Obstructed or absent breathing○ Central cyanosis○ Severe respiratory distress○ Shock/impaired perfusion○ Coma/reduced consciousness○ Convulsions○ Severe dehydration○ Clinical concern that the child is in an emergency stateBlood glucose 2.5–5.0 mmol/L at arrival to the emergency department (3.0–5.0 mmol/L for severely malnourished children)

#### Exclusion criteria

Children with a known diagnosis of diabetesRefusal to participate by the child

### Blood glucose testing

Capillary blood glucose levels will be measured using the HemoCue Glucose 201 point of care device, which has shown reliable performance [19]. Quality control will be done by regular controls with standardised glucose fluids.

### Randomisation and group allocation

Randomisation will be to the two arms of the trial: the intervention arm and the control arm. Children with severe malnutrition will be randomised separately in another stratum to ensure the same number of children in each arm of each stratum. An independent statistician who is not part of the research team has produced a computer-generated randomisation list using a two-stage process to ensure allocation concealment. The computer first randomly selects whether the block will contain six or eight patients and then randomly chooses one of the possible different allocation blocks for the selected size.

The investigators assign the subject identification numbers sequentially and group allocation is determined when the research staff opens an opaque envelope prepared in advance by the independent trial statistician. Envelopes are opened in the emergency department as soon as a child has been identified as eligible for the trial. The study identification number will be retained throughout the study and will appear on all case report form pages and source documents.

### Sample size calculations

The required sample size using the following assumptions:a 1:1 intervention: control ratioA power of 0.80Significance level 0.05Mortality in control group: 15.4%Mortality in intervention group: 10.0%

is calculated to be 1266 children aged < 5 years, 633 in each arm. Assuming that 35% of children with an emergency sign present with low-glycaemia (unpublished data from Queen Elizabeth Central Hospital), and around 10% will refuse to participate, the total number to be screened is 4000.

### The intervention

Children in the intervention group will immediately receive a bolus of intravenous 5 mL/kg 10% dextrose, prepared using one part 50% dextrose and four parts 0.9% sodium chloride, (Ringer’s Lactate will be used instead of sodium chloride in severely malnourished children, in accordance with current local procedures). If intravenous cannulation is not possible after 15 min of attempting cannulation, then an intraosseous needle will be sited and used until intravenous cannulation is possible. Dextrose administration will continue as a maintenance infusion of intravenous 10% dextrose for 24 h, prepared using one part 50% dextrose and four parts 0.9% sodium chloride (Ringer’s Lactate for malnourished children) at standard maintenance rates (over 24 h: 100 mL/kg for the first 10 kg body weight, then 50 mL/kg for the next 10 kg, thereafter 25 mL/kg for each subsequent kg). If the clinical condition allows, the child will be given oral nutrition in accordance with current local procedures. Capillary blood glucose monitoring will be repeated at 30-min intervals, in line with ETAT recommendations for hypoglycaemia, with repeated equivalent doses given until levels reach ≥ 5.0 mmol/L. Severely malnourished children will be treated according to WHO guidelines with nasogastric rehydration as the first option, in accordance with local procedures.

All children in the control group will be kept in the emergency department for a minimum of 60 min and have their vital signs checked at discharge from the emergency room to the ward. If their clinical condition deteriorates they will be re-examined by clinical staff. Re-checking of blood glucose may be done if clinically warranted and, if found, hypoglycaemic dextrose infusion in a control child will be documented. The total amount of dextrose given during the admission will be documented for all enrolled patients to allow for comparison of received dextrose between control and intervention groups. Usual care—the care that is currently provided in the hospital—will be provided. This includes care according to local departmental guidelines that are based on the WHO’s ETAT guidelines [18] and definitive treatment of infective causes with antibiotics and/or antimalarial drugs. In contrast to the intervention group, children with low-glycaemia will not receive any bolus dextrose or routine re-checking of their blood glucose level. Figure 1 provides a flowchart of the study.

**Fig. 1 Fig1:**
[figure not shown]
Study *flowchart*

### Primary and secondary outcome measures

The primary outcome is in-hospital mortality. Secondary outcome is 24-h mortality. Follow-up will continue until discharge from hospital or death. The expected trial target is superiority of dextrose treatment in the intervention group compared to the control group. Figure 2 provides a schedule of enrolment, interventions and assessments in the study, according to SPIRIT guidelines.

**Fig. 2 Fig2:**
[figure not shown]
SugarFACT schedule of enrolment, interventions and assessments

### Data collection and management

Electronic clinical record forms (CRFs) have been developed from the paper drafts with the assistance of Malawi College of Medicine Research Support Centre’s Data Management team using Open Data Kit (https://opendatakit.org). Data are collected on Android tablets and uploaded to a database on the day of collection. The data management team provides the investigators with weekly data reports including numbers enrolled and any problems in data collection including serious adverse events (SAEs) and protocol violations. Details about the data management plan are in the Data Management Standard Operating Procedures, which can be requested from the study team. Data access will be granted to investigators and the assigned study statisticians with whom a Mutual Confidential Disclosure Agreement has been signed (available upon request from corresponding author). Data will be exported for analysis to a statistics software package such as STATA v 12 for analysis. Principal analysis will be on an intention-to-treat principle and all statistical analysis will be done by a statistician who is independent from the study research team.

### Analysis plan

Collected data will undergo the following hypotheses testing and analysis:I.H_0_: Children in the intervention group have the same in-hospital mortality as children in the control group.

Analysed by intention-to-treat using logistic regression at a significance level of 0.05. Sub-group analyses will be performed on the a priori-defined groupsII.H_0_: Children in the intervention group have the same 24-h mortality as children in the control group.

Analysed by intention-to-treat using logistic regression at a significance level of 0.05. Sub-group analyses will be performed on priori-defined groups. Details about the analysis are in the Statistical Analysis Plan, which can be requested from the study team.

### A-priori defined sub-groups

#### Sub-group for stratified randomisation

Severe malnutrition: mid-upper arm circumference < 115 mm (< 110 mm if aged < 6 months) or clinician’s diagnosis (oedema of both feet, severe wasting, hair changes, dermatitis)

#### Sub-groups for sub-group analyses

Body temperature ≥ 38.5 °C at admissionAge < 12 monthsAge < 24 monthsBlood glucose < 3 mmol/LBlood glucose < 4 mmol/LConfirmed malaria by blood slideConfirmed bacterial infection by positive blood cultureInability to feed before admissionGuardian’s report of poor nutritional intake before admissionTrauma or surgery as reason for admissionSevere acute malnutrition

Primary analysis will be by intention-to-treat. Per-protocol analyses will also be conducted and the number of children who do not follow protocol will be reported. Protocol violations include, in the intervention group: failure to give an initial dextrose bolus; failure to repeat the blood glucose test after 30 min; failure to give a repeat dextrose bolus; failure to prescribe or to start the dextrose infusion or oral nutrition; incorrect dose of dextrose. And in the control group: admission to the ward < 60 min after enrolment; additional blood glucose testing or dextrose administration in the emergency department. Protocol violations are included in the weekly data report from the data manager.

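### Clinically warranted glucose re-checks and treatment of hypoglycaemia in controls are allowed in one section of the protocol article and listed as protocol violations in another, so the per-protocol control group may lose deteriorating children

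*Protocol article*

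**What the plan says.** **Control care (Protocol article, The intervention).** Controls stay in the emergency department for at least 60 minutes and are re-examined by clinical staff if they deteriorate. "Re-checking of blood glucose may be done if clinically warranted", and dextrose given to a control found hypoglycaemic is to be documented. What the section withholds from controls with low-glycaemia is bolus dextrose and routine re-checking.

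**Violations (Protocol article, Sub-groups for sub-group analyses, closing paragraph).** "Primary analysis will be by intention-to-treat". The article adds: "Per-protocol analyses will also be conducted and the number of children who do not follow protocol will be reported". The control-arm violations listed are ward admission before 60 minutes and "additional blood glucose testing or dextrose administration in the emergency department". The intervention-arm violations include "failure to repeat the blood glucose test after 30 min", and failures to give the initial or a repeat bolus or to start the infusion or oral nutrition. Violations also go into the data manager's weekly report.

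**The concern.** The list does not separate a warranted re-check from an unwarranted one, or treatment of hypoglycaemia from dextrose given for low-glycaemia alone. The ordinary meaning of an additional test is any test after the one at arrival, so a control who deteriorates, is re-tested and is treated appears in the violation count although the protocol was followed.

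Two outputs are at stake. The reported number of children who did not follow protocol would mix real departures with permitted care. And if violators are excluded, membership of the per-protocol control group depends on how the child fared after randomisation. Deteriorating controls would be expected to die more often than the rest, so removing them lowers control mortality and makes dextrose look worse even if it does nothing. The trial is not blinded, so the decision to re-test a control is also taken with the allocation known.

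**Working it through.** **1. The two sections side by side**

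| Event in a control in the emergency department | The intervention | Violation list |
|---|---|---|
| Routine glucose re-check | Not done | Violation: consistent |
| Re-check because clinically warranted | Allowed | Violation: contradiction |
| Dextrose after hypoglycaemia is found | Foreseen, to be documented | Violation: contradiction |
| Bolus for low-glycaemia alone | Withheld | Violation: consistent |
| Ward admission before 60 min | Not allowed, no exception given | Violation: consistent |

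The conflict is confined to the second and third rows. It is a real overlap, because controls spend at least 60 minutes in the place where the violation is defined.

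**2. The plan's own figure**

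Sample size calculations gives control mortality 15.4%, intervention mortality 10.0%, power 0.80, significance level 0.05 and 1:1 allocation; the result "is calculated to be 1266 children aged < 5 years, 633 in each arm". The two-sided two-proportion formula with continuity correction gives 633 per arm, 2 × 633 = 1266, an exact match. (Without the correction it gives 596 per arm.) The point does not touch this figure. It supplies only the arm size and the control mortality used below.

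**3. Illustration of the control-arm effect**

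Inputs from the document: 633 per arm and 15.4% mortality, set equal in both arms so that there is no true effect. Assumed inputs, because the document gives none: the share *s* of controls dropped (5% to 10%) and the mortality *m* among them (35% to 40%). The Background quotes mortality of up to 42% in hypoglycaemic children. That makes 35-40% conceivable for controls found hypoglycaemic, but it is not an estimate for every re-tested child.

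Per-protocol control mortality = (0.154 − *s* × *m*) / (1 − *s*).

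Spurious OR (intervention/control) = [0.154/0.846] / [odds of per-protocol control mortality], where 0.154/0.846 = 0.1820.

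| *s* | *m* | Controls dropped | Control mortality left | Spurious OR |
|---|---|---|---|---|
| 5% | 35% | 32 | (0.154 − 0.0175)/0.95 = 14.4% | 1.08 |
| 5% | 40% | 32 | (0.154 − 0.0200)/0.95 = 14.1% | 1.11 |
| 10% | 35% | 63 | (0.154 − 0.0350)/0.90 = 13.2% | 1.19 |
| 10% | 40% | 63 | (0.154 − 0.0400)/0.90 = 12.7% | 1.26 |

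By normal approximation, with 633 intervention children and 633 × (1 − *s*) controls, a nominal two-sided 5% test would reject about 8% of the time in the first row and 28% in the last. If the dropped children had the same 15.4% mortality as the rest, the OR would be 1.00: the bias comes from the link between being re-tested and dying, not from the loss of numbers.

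**The case against.** **Only a secondary analysis is affected.** Both hypotheses are tested by intention-to-treat, and the per-protocol analysis is additional. This stands and limits the severity.

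**The article never says that each violation removes a child.** The list is open-ended, it also serves reporting, and the definition of the set may be in the unseen analysis plan. This stands too: exclusion is the usual meaning of per-protocol, not a stated rule. The contradiction about what counts as a violation, and its effect on the violation count, does not depend on it.

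**Excluding controls who received dextrose is a common per-protocol choice.** That is fair as a deliberate and stated choice. It does not explain why a re-test alone, without dextrose, should count.

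**Stronger readings that the document does not support.** A reader might infer three further things.

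- *That ward transfer before 60 minutes is also permitted care wrongly counted.* It is not: The intervention gives no clinical exception to the 60-minute stay, and the two sections agree.
- *That an intervention child at target after one bolus is a violator for lack of a second.* The intervention already ties repeat doses to glucose not having reached the stated target, so no repeat was due.
- *That early intervention deaths are dropped, making dextrose look protective.* This needs a literal reading of failure to perform a step as covering a child already dead, together with the unstated exclusion rule. The article is silent on such children; it does not call them violators.

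Even if early deaths were dropped, the two exclusions would pull in opposite directions. Removing early deaths equal to 2-3% of the intervention arm leaves (0.154 − 0.02)/0.98 = 13.7% to (0.154 − 0.03)/0.97 = 12.8% mortality there. Set against 10% of controls dropped with 35-40% mortality, the OR runs from 0.96 to 1.09. Opposing biases do not make the analysis valid, but no net direction can be claimed under that reading.

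**Conclusion.** The contradiction on control-arm testing and treatment is real and stands on the printed text. It certainly muddies the violation count. If violators are excluded in the usual way, it also selects the per-protocol control group on deterioration. The odds ratio of 1.08 to 1.26 in the working is an illustration resting on assumed shares and mortality, not an estimate. It would shrink towards 1 if few controls were re-tested or if those re-tested were not much sicker than the rest. Nothing confirmatory is affected. Severity is minor to moderate: worth correcting because the correction is cheap and the per-protocol result will be read beside the primary one.

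**What to change.** Reconcile The intervention with the violation list. The change concerns classification for analysis only and takes no position on what care a child should receive.

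1. **Control arm.** Record each re-check or dextrose treatment in the emergency department with its reason. State that a clinically warranted re-check, or treatment of documented hypoglycaemia, is not by itself a violation that removes the child from the per-protocol set. A sensitivity analysis may exclude controls given dextrose, labelled as such. Leave the early-transfer item as it is.
2. **Intervention arm.** State that a step counts as failed only if it was due, so that a child who died before it fell due stays in the set. This settles in one sentence what the article leaves open.
3. **Reporting.** Give the number of controls re-tested or treated for a recorded clinical reason separately from the violations.

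Cost: a paragraph in the protocol or analysis plan, and possibly one reason field in the electronic record form if it has none. No change to sample size, procedures or the primary analysis.
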